#### Cost-effectiveness analysis

A cost-utility analysis with a health system perspective will be conducted in line with the methodological recommendations suggested by Lopez-Bastida et al. [60], and the guidelines defined in the economic evaluation literature [19, 61].

The study will be conducted considering the costs and the health effects of the intervention. Only direct costs of the program will be identified and valued. As direct costs for both groups, the drugs consumption, primary care visits, and hospital admissions will be considered. In the intervention group, the time dedicated by sport professionals of the exercise program will also be considered. Their total remuneration will be calculated based on the collective agreement for these professionals. First, for each group (intervention and control) an average of cost and effectiveness (the mean QALYs gained) will be calculated. Secondly, the ICER [19] will be calculated. To analyse the uncertainty in model parameters and verify the robustness of the ICER, various deterministic and probabilistic sensitivity analyses will be held [62]. The probabilistic analysis will be carried out through bootstrapping non parametric methods with 1000 replications. The resulting 1000 ICER replications will be plotted on the cost-effectiveness plane and will be used to construct an acceptability curve [63]. The cost-effectiveness plane is a graphical way of presenting cost-effectiveness results, with the difference in costs on the vertical axis and the difference in health benefits on the horizontal axis. Since incremental costs and health benefits can both be either positive or negative, there are four possible combinations, which will be reflected in the four quadrants of the cost-effectiveness plane:Upper-left quadrant: intervention less effective and more costly than comparator.Lower-left quadrant: intervention less effective and less costly than comparator.Upper-right quadrant: intervention more effective and more costly than comparator.Lower-right quadrant: intervention more effective and less costly than comparator.

The acceptability curve represents the proportion of simulations in which the intervention was considered cost-effective over a range of values of the threshold cost- per-QALY [64]. All analyses will be conducted in Stata v.13 (Stata Corp, College Station, TX, USA).

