### Interventions

The participants randomly assigned to the usual care (control) group will receive general advices from primary care centre medical staff about the positive effects of physical activity. The researchers will give 4 conferences (1 per month) explaining the benefits of exercise for longevity, prevention and treatment of diseases, the benefits of the Mediterranean diet, nutritional education, ergonomic advises, exercise to perform at home (e.g. stretching, strength training) and strategies to increase their daily physical activity levels.

The exercise intervention will be performed in four groups so that each group will comprise 15–20 participants. The groups will train 3 days/week (60 min per session) for a 16-week period at the primary care centre of Granada. The exercise intervention will meet the training standards of the American College of Sports Medicine [17] for adults. The exercise sessions will be designed, carefully supervised, guided and instructed by qualified exercise professionals.

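### The ICER charges delivery staff time to the exercise arm only, although controls receive four researcher-led conferences, so control cost and control QALYs do not describe the same comparator

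*Protocol article*

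**What the plan says.** All references are to the protocol article.

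- **Cost-effectiveness analysis, perspective and scope.** "A cost-utility analysis with a health system perspective will be conducted", and "Only direct costs of the program will be identified and valued".
- **Cost-effectiveness analysis, items by arm.** For both arms: "As direct costs for both groups, the drugs consumption, primary care visits, and hospital admissions will be considered". For exercise only: "In the intervention group, the time dedicated by sport professionals of the exercise program will also be considered". That staff time is to be valued from the professionals' collective agreement.
- **Interventions, control arm.** "The participants randomly assigned to the usual care (control) group will receive general advices from primary care centre medical staff". The same paragraph continues: "The researchers will give 4 conferences (1 per month) explaining the benefits of exercise for longevity". The other topics are diet, ergonomics, exercises for the home and ways to be more active each day.
- **Interventions, exercise arm.** "The exercise intervention will be performed in four groups so that each group will comprise 15–20 participants". Each group trains for one hour, three times a week, for 16 weeks.
- **Primary outcomes.** The ICER is the difference in mean cost between the arms divided by the difference in mean QALYs, with QALYs based on the participants' EQ-5D-5L responses.

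**The concern.** An ICER compares two courses of action, and each must have its cost and its effect measured for the same thing. Here the control QALYs come from women who were offered four conferences meant to change their behaviour. The control cost is built from drugs, visits and admissions, none of which contains the time of the people who gave those conferences. The general advice from medical staff can plausibly be captured through primary care visits. The conferences cannot, because the researchers give them.

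This is more than detail left to a fuller document. The article gives an explicit list by arm and adds delivery staff time for one arm only. An analyst who follows the list will pair the effect of a comparator with conferences with the cost of a comparator without them. The ICER is the trial's only primary outcome.

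**Working it through.** The plan states no cost figure, so there is none to reproduce. The check has two parts.

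**1. Which side of the ratio is affected**

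Let C and Q be mean cost and mean QALYs as the plan measures them, with E for exercise and C for control. Let *k* be the conference delivery cost per control woman and *q* the mean QALY effect of the conferences. The plan computes

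ICER = (C_E − C_C) / (Q_E − Q_C), where C_C excludes *k* and Q_C includes *q*.

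- *Reading A: the conferences are part of the comparator.* The consistent numerator is C_E − (C_C + *k*). The plan's numerator is too large by *k*. The denominator is right.
- *Reading B: the conferences are trial activity outside usual care.* Leaving out *k* is then right, but the consistent denominator is Q_E − (Q_C − *q*). The plan's denominator is too small by *q* if the conferences help. Any change they cause in drug use or visits also sits in C_C.

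The ratio is internally consistent under neither reading, unless *k* (reading A) or the conferences' effects (reading B) are negligible. The document does not say which reading applies.

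**2. Size under reading A**

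From the Interventions section: 4 exercise groups, 3 sessions a week, 16 weeks, 1 hour per session; 4 conferences. From Sample size: 75 women per arm.

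Assumed, because the document does not state them: one professional per exercise session; conferences of 1-2 hours; each given once; equal hourly pay; contact time only in both arms.

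- Exercise contact hours: 4 × 3 × 16 × 1 = 192 h, or 192 / 75 = 2.56 h per woman.
- Conference hours: 4 × 1 = 4 h to 4 × 2 = 8 h, or 4 / 75 = 0.05 to 8 / 75 = 0.11 h per woman.
- Share of exercise staff time: 4 / 192 = 2.1 % to 8 / 192 = 4.2 %.

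Varying the assumptions:

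| Conference deliveries | Hours | Pay ratio 0.5 | Pay ratio 1 | Pay ratio 2 |
|---|---|---|---|---|
| 4 talks, once each, 1 h | 4 | 1.0 % | 2.1 % | 4.2 % |
| 4 talks, once each, 2 h | 8 | 2.1 % | 4.2 % | 8.3 % |
| 4 talks, four audiences, 1 h | 16 | 4.2 % | 8.3 % | 16.7 % |
| 4 talks, four audiences, 2 h | 32 | 8.3 % | 16.7 % | 33.3 % |

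The pay ratio is conference pay divided by exercise pay. Each entry is hours × pay ratio / 192. The last two rows need each talk to be repeated for four audiences, which nothing in the text indicates; four conferences at one a month reads most naturally as four deliveries. More than one professional per session would lower every entry.

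These are shares of the staff-cost difference. They carry over to the ICER only so far as staff time makes up the difference in total cost. If savings on drugs, visits or admissions offset the exercise staff cost, the share of the net difference would be larger.

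**The case against.** The strongest case on the other side has four parts.

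- **The omission may be deliberate and correct.** The perspective is the health system, the comparator is called usual care, and the researchers, not the medical staff, give the conferences. If the health system would not fund them, their cost does not belong to usual care. This stands as a possible reading. It does not remove the mismatch, because the control QALYs then reflect more than usual care.
- **The net direction is open.** A reader might infer that the plan biases the ICER against exercise. The document does not support that. The weights and resistance bands described for the sessions and the telephone calls after missed sessions are also absent from the cost list, and leaving them out understates the exercise cost. The stated direction holds only for the conferences taken alone.
- **The size is small and rests on assumptions.** This stands. Length, repetition and pay are not given. A reader might also take the upper figures of 8-17 % at equal pay as likely, but they require repeated deliveries that the text does not mention.
- **Adding preparation time for the conferences only would be uneven.** This stands too. The exercise professionals also design their sessions, and the costing rule may or may not include that time.

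The planned deterministic sensitivity analyses could hold a test of this point, but the document does not name one.

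**Conclusion.** The point holds in a limited form. The listed cost items leave out the delivery of a control programme whose effect is counted, so the two sides of the ICER do not describe one control condition. With the conferences inside the comparator, and other things equal, the omission overstates the incremental cost by about 2-4 % of exercise staff cost. That figure assumes four single deliveries of 1-2 hours, one professional per session, equal pay and contact time only. With the conferences outside the comparator, the fault lies in the control QALYs, and the document gives no means of sizing it.

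Nothing here shows that the ICER as a whole is overstated, or that a conclusion on cost-effectiveness would change. The point deserves action because it concerns the sole primary outcome and is cheap to settle before analysis.

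**What to change.** In the Cost-effectiveness analysis section:

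1. State that the comparator is the control condition as delivered, conferences included.
2. Add the staff time of the four conferences to the control arm's costs in the base case, valued by a stated wage method.
3. Treat preparation time the same way in both arms: counted for both the conferences and the exercise sessions, or for neither.
4. Report one deterministic scenario without the conference cost, and state beside it that its control QALYs still include any effect of the conferences.

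The cost is one more cost line and one more scenario within sensitivity analyses already planned. No new participant data are needed; the research team gives the conferences and can record the hours.

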Each exercise session will include a 10 min warm-up period with walks and mobility exercises, followed by 40 min of a main part which will vary across week days (i.e. 3 different models of session). Sessions will finish with a 10 min cool-down period of stretching and relaxation exercises. The three model sessions will be: (i) First session of the week will involve circuit training including resistance exercises in a stepped progression during the program. Resistance circuit training will include 2–3 set of 6–10 exercises. The participants will perform 10–20 repetitions of multi-joint exercises and/or single joint exercises targeting major muscle groups such as biceps curls, triceps extensions, arm side lifts, shoulder elevations, chest press, lateral leg elevations, stands up from seated position, lunge, sideways lunge and step-up/step-down, squads, lower back extensions, abdominal crunch/curl-up and calf raises among others. Participants will carry out bodyweight exercises at the beginning of the program and, if it is necessary, free weights (0.5–3 kg barbells) and resistance bands will be used to reach the optimal intensity. The load will be gradually increased and each participant will individualize her effort to reach the intensity designed for each session; (ii) Second session of the week will include balance-oriented activities (position changes, monopodal and bipodal stances, backwards walks, …) and dancing (aerobic exercises); (iii) Third session of the week will combine aerobic, resistance strength and coordination exercises.

Heart rate will be measured with heart rate monitors (Polar Electro OY, Finland) to control the intensity of the sessions. One third of the participants in the intervention group will wear heart rate monitors in 1/3 of the sessions, both randomly selected. We will monitor the ratings of perceived exertion (RPE) using the Borg 6-20 RPE scale [18] during all the sessions. Intensity (expressed as RPE) will be expected to range from 12 to 16. The exercise volume and intensity programmed is shown in Table 2.

**Table 2 Tab2:** Exercise intervention

Sesion structure	Content								
Warm-up 10’ minutes	Joint mobility and different walk modalities								
Conditioning 40 min	Week	1-2	3-4	5-6	7-8	9-10	11-12	13-14	15-16
	Intensity RPE	12-13	12-13	13-14	13-14	14-15	14-15	15-16	15-16
	Monday								
	Resistance training circuit*	6 exercises	8 exercises	8 exercises	8 exercises	8 exercises	8 exercises	10 exercises	10 exercises

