	Set x repetitions	2 × 15	3 × 15	3 × 18	3 × 20	3 × 18	3 × 15	3 × 12	3 × 10
	Wednesday	Choreographies and aerobic exercises							
	Friday	5 exercises	6 exercises	6 exercises	6 exercises	7 exercises	7 exercises	8 exercises	8 exercises
	Resistance exercises (RE)^a^ and aerobic exercises (AE)^b^	2RE + 1AE + 2RE	3RE + 1AE + 2RE	3RE + 1AE+ 2RE	3RE + 1AE+ 2RE	2RE + 1AE + 2RE +1AE + 1RE	2RE + 1AE+ 2RE + 1AE + 1RE	2RE + 1AE + 2RE +1AE +2RE	2RE +1AE + 2RE +1AE + 2RE
Cool-down 10 min	Stretching and relaxation exercises								

RPE, rating of perceived exertion; *The circuit is composed of trunk, upper and lower extremities exercises. Body-weight, free weights (0.5–3 kg barbells) and resistance bands exercises. The load will be gradually and individualized increased for each participant to reach the intensity designed for each session; ^a^The set and repetitions in resistance exercise will be the same than the resistance circuit training;^b^ The aerobic exercise will have a duration between 2–4 min

To maximize adherence, several strategies will be implemented including music in all sessions, individualized attention during the intervention sessions, and telephone calls following non-attendance. The researchers will control and register the presence of adverse event during and between classes.

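### The cost list for the primary ICER leaves out delivery resources that only one arm receives: premises and equipment for exercise, and four conferences for control

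*Protocol article*

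**What the plan says.** The Cost-effectiveness analysis section sets the perspective: "A cost-utility analysis with a health system perspective will be conducted". It then limits the scope: "Only direct costs of the program will be identified and valued".

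The items follow. For both arms: "As direct costs for both groups, the drugs consumption, primary care visits, and hospital admissions will be considered". For the exercise arm alone: "In the intervention group, the time dedicated by sport professionals of the exercise program will also be considered". That time is to be valued from the professionals' collective pay agreement. No other programme resource is listed.

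The Interventions section describes more than this.

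- **Exercise arm:** four groups train three times a week, 60 minutes a session, for 16 weeks at the primary care centre. Where needed, free weights "and resistance bands will be used to reach the optimal intensity". Heart rate monitors are worn by a third of the women in a third of the sessions. Adherence measures include "telephone calls following non-attendance".
- **Control arm:** besides general advice from centre staff, "The researchers will give 4 conferences (1 per month) explaining the benefits of exercise for longevity", with diet, home exercise and ways to be more active also covered.

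The Primary outcomes section defines the ICER as the difference in mean cost divided by the difference in mean QALYs.

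**The concern.** The cost list is narrower than its own scope statement. Premises and equipment are direct costs of running the programme. A health system that adopted it would have to supply them, and the Discussion presents the programme as readily transferable.

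The control arm has a separate mismatch. Any benefit of the conferences counts in the control women's QALYs, but the conferences have no cost. The protocol does not say whether they belong to routine care or exist only for the trial. The Abstract calls this arm usual care, and the Randomization and blinding section calls it non-exercise, yet it receives monthly education that includes exercises to do at home.

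Each omitted item falls in one arm only, so none of them cancels from the cost difference. The QALY difference that can build up over 16 weeks is very small, so a modest cost per woman becomes a large amount per QALY in the trial's primary result.

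**Working it through.** **1. The plan's own figure.** Inputs from Sample size: EQ-5D difference 0.07, SD 0.12, power 90 %, α 0.05 (two-sided assumed).

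n per group = 2 × (1.960 + 1.282)² × 0.12² / 0.07² = 61.8, so 62 per group and 124 in total. This reproduces the stated figure; power at 62 per group is 90.1 %. The plan states no QALY difference and no unit costs.

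**2. QALY difference implied by 0.07.** EQ-5D is measured at 0, 8 and 16 weeks. The QALY difference is the area between the two arms' curves, in years. The path is an assumption, so four are shown, with the ICER shift for an illustrative 10 currency units per woman left out of one arm (10 / QALY difference):

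| Path of the 0.07 difference | Calculation | QALY difference | ICER shift per 10 units |
|---|---|---|---|
| Linear over weeks 0–16 | 0.07 × 0.5 × 16/52 | 0.0108 | 929 |
| Full by week 8, then held | 0.07 × (0.5 × 8 + 8)/52 | 0.0162 | 619 |
| Present from day 1 | 0.07 × 16/52 | 0.0215 | 464 |
| Opens only after week 8 | 0.07 × 0.5 × 8/52 | 0.0054 | 1,857 |

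**3. Direction, if exercise gains QALYs.** Leaving out premises, equipment and monitors understates exercise cost and lowers the ICER. Leaving out the conferences understates control cost and raises it.

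**4. Rough scale of the items.** From Interventions: 4 groups × 3 sessions × 16 weeks × 1 h = 192 instructor hours, or 192/75 = 2.56 h per woman with 75 women in the arm, assuming one instructor per group and no preparation time.

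The length and repetition of the conferences are not given. Assume between 4 h (1 h each, given once) and 32 h (2 h each, repeated for four subgroups). That is 4/192 = 2 % to 32/192 = 17 % of instructor time. With an assumed rate of 15–30 per hour and the linear path (0.0108 QALY):

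- Instructor time, which is counted: 15 × 2.56 = 38.4 to 30 × 2.56 = 76.8 per woman, or about 3,570 to 7,130 per QALY.
- Conferences, not counted: 15 × 4/75 = 0.8 to 30 × 32/75 = 12.8 per woman. Adding them lowers the ICER by about 74 to 1,190 per QALY.
- Room and equipment, not counted: at an assumed 5 to 50 per woman, adding them raises the ICER by about 464 to 4,643 per QALY.

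The hourly rate and the 5–50 range are assumptions, used only to show scale.

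**5. Planned sensitivity analyses.** The bootstrap resamples recorded costs, so it cannot reflect items that were never costed. Deterministic analyses are planned, but none is tied to a cost item.

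**The case against.** The strongest defence is that this is a condensed article. Unit costs and costing conventions normally sit in a fuller economic plan, and the section defers to published guidance. Whether to charge for a room in an existing centre is a convention. Weights and bands are used only if needed, are cheap, and are reused across groups. The conferences are given by researchers, so leaving out trial-only activity is defensible. All these items could also be costed afterwards from the fixed design.

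Much of this stands as a limit on size. It does not remove the point, because the article does more than omit detail: it states the scope and names the items, and those items do not cover what the arms receive. No exclusion is justified.

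Several stronger readings are tempting but unsupported:

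- *The omitted resources are common to both arms.* They are not; if they were, they would cancel from the numerator.
- *The ICER is biased in favour of exercise.* The omissions pull in opposite directions, and no unit costs are given.
- *The conferences are the main problem.* Under the assumptions above they are small beside instructor time.
- *The adherence calls are uncosted.* They may fall within the professionals' time; the text does not say.
- *All specialist and emergency contacts are already extracted but ignored.* The Socio-demographic and clinical information section says only that the number and reason of medical visits will be looked up in the medical database. It does not say which kinds of visit are recorded there.

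**Conclusion.** The point holds in limited form. Followed as written, the cost list leaves premises, weights, bands and heart rate monitors out of the exercise arm's cost and four conferences out of the control arm's. All are delivery resources that the protocol itself describes, and each belongs to one arm.

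What can be quantified is leverage, not bias. Each 10 currency units per woman omitted from one arm moves the ICER by about 930 per QALY if the 0.07 difference opens linearly, and by about 460 to 1,860 across the paths considered. This rests on the planning difference being the true one and on a 16-week horizon. The net direction and size of the error cannot be determined from the document. Leaving out the conferences would be acceptable if they were declared trial-only, which the protocol does not do.

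**What to change.** In the Cost-effectiveness analysis section:

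1. List and value delivery resources by arm. Exercise: instructor time (stating whether it covers the adherence calls), room use, and equipment including the monitors. Control: staff time and room for the four conferences.
2. Name a deterministic scenario with conference cost set to zero, for the case that the conferences are trial-only.
3. State which visit types count. Include specialist and emergency visits in both arms where the medical database records them.
4. Describe the comparator as usual care plus monthly education in the aims and conclusions.

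The cost is some wording, a short unit-cost table, and a log of room hours, conference hours and calls kept as they occur. The downside is a few extra unit costs to find, and an ICER that may move either way.

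### The cost list for the primary ICER names only sport professionals' time as a delivery cost, leaving out premises and training equipment, so the incremental cost of exercise is understated by an amount the article does not allow one to determine

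*Protocol article*

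**What the plan says.** The Cost-effectiveness analysis section of the protocol article adopts a health system perspective and sets the scope: "Only direct costs of the program will be identified and valued". It then lists the items. For both arms: "As direct costs for both groups, the drugs consumption, primary care visits, and hospital admissions will be considered". For the exercise arm it adds one more: "In the intervention group, the time dedicated by sport professionals of the exercise program will also be considered". The valuation is by pay: "Their total remuneration will be calculated based on the collective agreement for these professionals".

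The Interventions section describes what delivery uses. Classes run "for a 16-week period at the primary care centre of Granada", three times a week for 60 minutes, in four groups of 15–20 women. Sessions start with bodyweight work, and where needed free weights "and resistance bands will be used to reach the optimal intensity". The adherence strategy includes music, "individualized attention during the intervention sessions, and telephone calls following non-attendance". In the control arm, "The researchers will give 4 conferences (1 per month) explaining the benefits of exercise".

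Under Primary outcomes, the ICER is the difference in mean cost divided by the difference in mean QALYs.

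**The concern.** The costing section says it values the programme's direct costs, but the only programme input it names is labour in one arm. By the article's own account the exercise arm also occupies rooms at a primary care centre and uses training equipment, and neither appears in the list. The control conferences are missing as well, but they are four events against 192 class hours.

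The cost difference is the numerator of the sole primary outcome, so leaving out mostly exercise-arm items pushes it one way. The Discussion presents the programme as cheap and readily transferable. A health system adopting it would need rooms and equipment as well as instructors. The denominator is also small, because it is a utility gain held for at most 16 weeks, so modest sums per woman become visible on the cost-per-QALY scale.

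**Working it through.** **Inputs from the protocol article**
- Four groups of 15–20, three 60-minute sessions a week, 16 weeks (Interventions).
- 75 women per arm; planned EQ-5D difference 0.07, SD 0.12, power 90 %, α 0.05 (Sample size).
- EQ-5D-5L at 0, 8 and 16 weeks, used for the cost-utility analysis (Quality of life, mental health and positive health).
- No unit price or total cost is given anywhere.

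**1. The plan's own figure.** A two-sided comparison of two means with these inputs gives 62 per group, 124 in total, as stated. This supports 0.07 as the planning effect. There is no stated cost figure to reproduce.

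**2. Uncosted room use.** 4 groups × 3 sessions × 16 weeks × 1 h = 192 class hours. Per woman: 192 / 75 = 2.56 h. With groups of 20 or 15 (80 or 60 women): 192 / 80 = 2.4 h or 192 / 60 = 3.2 h.

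**3. Control-arm offset.** There are four conferences. Their length is not stated. If each lasts 1–2 h and is given once to the whole arm (assumptions), they take 4–8 h, or 4 / 75 = 0.05 to 8 / 75 = 0.11 h per woman.

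**4. QALY difference at the planned effect.** This is the area under a 0.07 difference over 16 weeks, for three time courses:
- linear gain to week 16: 0.5 × 0.07 × 16/52 = 0.0108
- full gain by week 8, then held: 0.07 × (0.5 × 8/52 + 8/52) = 0.0162
- immediate full gain: 0.07 × 16/52 = 0.0215

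**5. Leverage.** ICER shift = net omitted cost per woman / QALY difference. Per EUR 1 omitted: 1 / 0.01077 = about EUR 93, 1 / 0.01615 = about EUR 62, and 1 / 0.02154 = about EUR 46 per QALY. This step needs no price assumption.

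**6. Illustration on assumed prices only.** Take rooms at EUR 5–30 per hour, equipment at EUR 5–20 per exercise-arm woman, and conferences at EUR 0–5 per control woman.
- Low end: 5 × 2.56 + 5 − 5 = EUR 12.8 per woman.
- High end: 30 × 2.56 + 20 − 0 = EUR 96.8 per woman.
- ICER shift: about EUR 1,190–8,990 per QALY (linear) or 590–4,490 (immediate).
- If the rooms have no opportunity cost, the net omission is 5 − 5 = EUR 0 to 20 − 0 = EUR 20 per woman. The shift is then EUR 0 to about 1,860 (linear) or 930 (immediate).

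The width of these ranges shows that the size is not determined by the documents.

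**7. Can the planned sensitivity analyses repair it?** Net monetary benefit at threshold λ is λ × ΔQALY − ΔCost. If a fixed sum c per woman is missing from ΔCost, every one of the 1,000 bootstrap replicates is too favourable by c, at every λ. The acceptability curve can therefore only be too high, never too low. Bootstrapping resamples recorded costs and cannot restore one that was never recorded. The deterministic analyses are not specified. They could vary programme cost, but only if room and equipment use had been logged.

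**The case against.** The strongest defence is that the omission is partly inferred. The restrictive word in the scope sentence limits costing to direct programme costs; it does not say that staff time is the only one. Equipment could fall under that general sentence. The section also commits to published economic-evaluation guidance, and a journal article may leave an itemised list to the full protocol. This has some weight. However, the article does itemise, down to how the pay is valued, and a reader following the list would not collect room or equipment costs.

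Other objections stand:
- Non-attendance calls and preparation may already lie within the professionals' costed time. Adding them separately could double count.
- The documents do not say whether the rooms are hired, displace other use or would be idle. Whether they carry an opportunity cost is open.
- Weights and bands are used only as needed, and their annuitised cost may be low. Heart rate monitors may be partly a research cost.
- No threshold or total cost difference is given against which a shift could be judged.

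A reader might infer that the omitted items are about as large as the labour cost, or that they make up a given share of programme cost. The documents do not support this: it rests entirely on assumed prices and on one instructor per class, whereas the article refers to professionals in the plural and does not state staffing per session. Nor can one infer that a conclusion on cost-effectiveness would change.

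**Conclusion.** The point holds in a limited form. As written, the base-case cost omits premises and training equipment in the exercise arm and the conferences in the control arm, and the net effect is to understate incremental cost. The acceptability curve then favours exercise. The ICER does so too, provided the QALY difference is positive; with a zero or negative difference the ratio cannot be read that way.

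The sensitivity is EUR 46–93 per QALY for each net EUR 1 per woman omitted, assuming the planned 0.07 difference and a time course between immediate and linear gain. The amount omitted cannot be found from the documents. It could be close to nil if the rooms have no opportunity cost and the equipment is cheap.

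This is a costing rule worth correcting before resource data are collected. It is not a flaw that invalidates the trial.

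**What to change.** Amend the programme-cost sentences of the Cost-effectiveness analysis section so that the base case covers delivery inputs in both arms:

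- all delivery staff time, stating that preparation and non-attendance calls fall within it so that they are counted once, and including the staff time of the control conferences;
- training equipment, annuitised over its useful life;
- premises, from logged room hours, valued at the health system's cost.

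Report two deterministic sensitivity analyses: one with rooms at zero opportunity cost, and one with the professional-time-only figure. Exclude research-only items such as outcome assessments.

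The cost is a short resource log (room hours, equipment invoices, staff hours) and a wording change. No participants or procedures are added. The ICER is likely to become slightly less favourable to exercise.
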